### Withdrawal criteria

Participating anaesthetists will be expected to act in the best interests of their patients, and so will be free to withdraw individual cases or to omit any aspect of the bundle (for example, the use of the filter) if they believe this is warranted. Participants will be free to withdraw from the study. They will be asked to report any such decisions to the investigators.

### Intervention

The intervention will involve the implementation of the bundle as outlined below. It is recognised that some participating anaesthetists may already include some of these elements in their normal practice, so the bundle is *supplementary to usual practice* in that *all* of its elements are considered essential in the active phase of the study. In either phase of the study, if an anaesthetist’s standard practices include other steps to improve aseptic practice, these should be followed as usual for that clinician.

### The infection prevention bundle

The bundle consists of the following steps:Wipe skin with alcohol (with or without chlorhexidine) and allow to dry before inserting any IV line.Inject all IV bolus medications except propofol through a 0.2-μm filter incorporated into each patient’s IV line (see Fig. 1 for example configurations):Use aseptic technique when attaching the filter to the IV line and, unless it has been freshly opened from sterile packaging, wipe the IV line injection port to which the filter will be attached with alcohol (with or without chlorhexidine) for 15 s and allow to dry.If the filter is moved from one access point to another during the case, the new access point should first be wiped with alcohol (with or without chlorhexidine) for 15 s and allowed to dry.Use more than one filter if necessary or desired (e.g. for cardiac patients, one filter in the peripheral line, one on a central line port where bolus medications may be given, and a third onto the medication injection port on the bypass machine for the perfusionist to use when administering medications).Remove the filter(s) on discharge from the Post Anaesthesia Care Unit or on admission to the Intensive Care Unit.3.Use a meticulous aseptic technique when drawing up or injecting propofol, and discard syringes, needles or the medication in the event of any suspected contamination:Note that the rubber bungs on propofol vials are not sterile even with the cap in place, so they should be wiped with alcohol (with or without chlorhexidine) for 15 s and allowed to dry before propofol is drawn up. If the medication is supplied in an ampoule, wipe the outside of the neck and surrounding part of the ampoule with alcohol (with or without chlorhexidine) before opening.Use a new needle or spike for each occasion.Cap the syringe with a syringe cap or capped needle.Administer as soon as possible and discard propofol after 1 h if not used.Do not reuse syringes or needles for propofol, even for the same patient.Flush the IV port with sterile sodium chloride 0.9% after propofol has been administered to ensure no residual propofol remains to support bacterial growth, using a meticulous aseptic technique to draw up the flush.4.Perform hand hygiene:Before and after interacting with each new patient (i.e. on entering the operating room and on leaving a patient in the Post Anaesthesia Care Unit)Before and after any procedure creating risk of infection (e.g. IV insertion, airway manipulation, administering propofol, etc.).After blood and body fluid exposure (e.g. intubation, IV line insertion, etc.); remove gloves (if they have been worn) and, if practicable, perform hand hygiene before spreading contamination to the work station, computer key board and other surfaces.5.Maintain clean working surfaces:Place used laryngoscopes, masks and other contaminated objects into a tray designated for this exclusive purpose; maintain strict separation of clean and contaminated areas — do not use this tray for clean instruments, swabs or other items even at the start of a procedure.Wipe the anaesthetic machine bench top and the circuit adjustable pressure valve with alcohol (with or without chlorhexidine) once the patient has settled into the maintenance phase of anaesthetic (i.e. after intubation of the trachea if this is done).

**Fig. 1 Fig1:**
[figure not shown]
Three examples of filter configurations for the ABC study. **a** filter and injection port with a 3-way tap to be attached to the IV line; **b** filter and injection port attached to a side port on the IV line; **c**, as in **b**, with a 20-mL syringe filled with sterile sodium chloride 0.9% (for easy flushing) attached via a 3-way tap. Any practical approach that permits injection of medications through a filter is acceptable. Note: in these pictures the lines and filter are not primed with fluid. Fig. 1 is our own

#### Notes

Specific notes regarding the infection prevention bundle are as follows:Propofol should not be injected through the filter.The filter has a dead space of 0.45 mL and the injection port has a dead space of 0.11 mL (= 0.56 mL in total); therefore, as with any IV setup, it is necessary to prime the filter with sterile sodium chloride 0.9% or sterile water for injection to eliminate air, and it is also necessary to ensure that medications are flushed through.Hand hygiene implies either hand washing with medicated soap and water or using alcohol-based hand rub; it is important for hands to dry properly.

Provided the medications are injected through a 0.2-μm filter, the study does not ask for hand hygiene in relation to the injection and drawing up of medications other than propofol (Fig. 1).

### Control (usual care)

For this study, usual care is defined as the practices usually used by each participating anaesthetist, notably in relation to asepsis. If a participating anaesthetist already uses some of the elements in the bundle, he or she should continue to do so.

### Both groups

It is expected that standard hospital policy will be followed in both groups with respect to:Operating room temperature controlSurgical antimicrobial prophylaxisSingle patient-use only for all medications and fluidsWiping the anaesthetic machine bench top and medication trolley top between each caseThe use of new or cleaned medication trays for each case.

It is expected that individual anaesthetists’ normal practice will be followed with respect to intraoperative oxygen concentrations and postoperative oxygen therapy.

### Implementation

The implementation will follow the principles of improvement science listed in Table 1.

### Development of educational and motivational material

The following resources have been developed:An Anaesthetists Be Cleaner (ABC) study website (http://abc.auckland.ac.nz/) which includes the study synopsis, online resources for the study and up-to-date information on the details and progress of the studyA laminated two-sided single sheet outlining the bundle as above and including Fig. 1. This will also be placed in all participating operating rooms with the agreement of the participating departments, and on the study websiteSets of slides (including versions for online viewing) supported by handouts for presentations to participating anaesthetists, outlining the study, its rationale and its interventionDemonstration videos contrasting ideal with imperfect practices in relation to the elements of the bundle. These have been made at the Simulation Centre for Patient Safety of the University of Auckland using highly realistic simulations of illustrative anaesthetic scenarios. The videos will be placed on the study websiteA register of participants who have attended educational sessions on the study and watched the online videos.

### Enrolment of departments and departmental champions

Support in principle for this study was obtained from senior leadership in each of the participating hospitals. After ethics approval was obtained, the standard institutional site approval was sought from each hospital, which included obtaining the formal support of each department. After these formalities have been completed, the support of the chief executive officers and chief medical officers of each hospital, and permission to cite this for the purposes of the study, will be confirmed in writing. An email outlining the study and seeking support for it, with a copy of the protocol, will then be sent (through departmental administrators) to the staff of all participating departments, including all relevant surgeons and nurses. This will include an invitation for questions to be asked or concerns to be expressed. A study information sheet will be placed on the research notice board at each study centre, with a link to the study website.

One or more champions have already been appointed in each participating department. These champions will take part in and support all presentations and communications about the study.

### Randomisation of departments

The five departments will be sequentially allocated in a random order to the five possible dates of the bundle implementation, as shown in Table 2.

**Table 2 Tab2:**
[figure not shown]
Implementation structure of the stepped wedge. *Shaded cells* indicate those steps and sites in which the intervention has been implemented

### Rollout of the bundle

The study will be rolled out sequentially across departments per the stepped wedge timetable outlined in Table 2. In the lead-up to each department’s rollout we will present the study to one or more departmental meetings (if necessary, further presentations will be made to technicians, perfusionists, nurses and surgeons, depending on interest, demand and availability to attend the primary presentations). At these presentations feedback will be sought on any ways to facilitate embedding the intervention, and questions will be invited. The aim will be to develop a sense of shared ownership and collaboration in implementing the bundle. The presenters will also inform participating anaesthetists and technicians that observational data pertaining to aseptic practices and adherence to the bundle once implemented will be collected. The anonymous nature of the data collected through observation will be emphasised.

Each department will be told of the date of the implementation of the bundle in the weeks leading up to that date. This is done to reduce the likelihood of a change in practice prior to the bundle implementation. During the weeks approaching the implementation date, communication with participating clinicians will be pursued to ensure that all relevant people are aware of the rollout. In particular, all participants will be sent one or more emails (through departmental administrators) reminding them of the planned rollout and inviting them to contact the investigators if they have any concerns or questions.

Posters promoting the study in general terms, and noting that observations may occur, will be placed in all participating departments and operating rooms several weeks prior to roll-out. These will have a section counting down the days to roll-out designed to alert all relevant people to the coming changes and to create some sense of anticipation and excitement. On the day of the rollout we will ensure that a poster with key elements of the bundle expressed in simple terms is placed in each relevant operating room and the post-anaesthesia care unit.

The study coordinator will liaise with the anaesthetic technicians in each department to ensure that the study consumables are available. For 4 weeks following the designated first day of the rollout, the study coordinator will be available in the operating rooms for at least some time each day to encourage the rollout, to deal with any difficulties and to answer any questions. Any practical difficulties will be recorded.

### Blinding, concealment and cross-contamination between study phases

Neither blinding nor concealment will be possible. The clusters have been chosen, in part, to minimise as far as possible any overlap of staff working in both control and active phases between sites. If this does occur, this will be noted and acknowledged as a limitation of the study.

### Outcomes and measures

Our interest in this study lies in demonstrating a reduction in clinically significant postoperative infections of any kind in our targeted high-risk patient group. Given our limited funding, we are not able to prospectively measure rates of infection ourselves, but we are able to access national and hospital databases of routinely collected relevant outcome data (see the following sections). In addition, we will collect observational data for each cluster both before and after implementation in order to assess changes in aseptic practices of anaesthesia team members over the period of the study.

#### Primary outcome

Our primary outcome variable will be days alive and out of hospital to 90 days (DAOH_90_). We have selected DAOH_90_ as our primary variable because:It is sensitive to any postoperative complication (including, but not limited to postoperative infection) that is sufficiently serious to require prolongation of hospitalisation or re-admission into hospital or early death.It is available from NZ’s national minimal dataset, and so can be readily collected for all patients.It is more powerful, statistically, than a binary measure (such as infection vs no infection).

With our cluster randomised study design it will be reasonable to attribute any reduction in DAOH_90_ following implementation of the bundle to a reduction in clinically important postoperative infections of any type, and our analyses will make allowance for potential confounding factors unrelated to the study.

#### Secondary outcome

Our secondary (explanatory) outcome will be the rate of specified postoperative infections, as defined and collected by the national surgical site infection surveillance programme for patients undergoing hip or knee arthroplasty or cardiac surgery.

#### Process measures

The aseptic practices of the participating anaesthesia teams will be measured using a simple behaviourally anchored rating scale (BARS) (see Additional file 2). This has been developed for the study and will have elements addressing each item in our bundle. The overall score on the BARS for each case will provide our primary process measure. In addition, we will record participation by anaesthetists and technicians in relevant presentations, and in watching or reading online resources.

### Statistics and sample size

DAOH_90_ data have a bimodal, left-skewed distribution that does not lend itself to parametric analysis. Data from a previous study of 20,000 general surgery procedures indicate that most patients score highly, so comparing measures of central tendency between groups can exclude the patients who are most likely to realise improved outcomes. Although our preference would be to use permutation testing methods, our five-cluster, five-sequence design only allows for 120 permutations. We consider this too low a number for a precise estimation of the significance of the difference between control and intervention cases. We will thus use a single Wilcoxon-Mann-Whitney *U* (WMWU) rank sum test as our omnibus test to ascertain whether intervention patients have significantly higher DAOH_90_ than control patients. This WMWU test will also be sensitive to prevailing trends in patient outcomes, so we will further investigate the difference using quantile regression. Models will be fitted at quantiles 0.1, 0.25, 0.5 and 0.75, with DAOH_90_ as the outcome, and time, intervention and site as the predictors. We will characterise any differences in distribution between groups by reporting differences associated with the intervention term in each model, and their significance.

We have used simulations to estimate our statistical power. Datasets were synthesised using distributions generated from four of our sites (excluding Starship Children’s Hospital) with different step lengths. Starship Children’s Hospital data were synthesised on the basis of the distribution from Auckland City Hospital’s cardiac unit. Distributions for each site were tweaked by increasing or decreasing the relative likelihood of higher DAOH scores until the desired magnitude of difference appeared at quantile 0.25. We found that a step length of 180 days (i.e. 6 months) would give us 100% power to detect a 2 DAOH difference at quantile 0.25 between groups using the WMWU and 77.7% power to detect an intervention effect using quantile regression (both two-tailed α < 0.05), with just over 10,000 patients. The intracluster correlation coefficient was measured as 0.02. Cluster sizes in the simulation depended on the ratio of caseloads between sites (see Table 2). Our study statistician has estimated that we will recruit 5492 cases in each group and will require 8454 filter units.

We note that the study is not powered to show a difference in our secondary outcome, surgical site infection. Reducing surgical site infections from a base rate of about 1.4% (a reasonable estimate of the overall rate at present) to 0.8% would require approximately 11,000 patients (5500 in each group, one-tailed α = 0.05 and β > 0.8: estimated with MedCalc [MedCalc Software, Ostend, Belgium]). If we allow for cluster allocation by assuming a design effect of 2.0 (intracluster correlation coefficient = 0.02), the required number is likely to be double this. Given the likely proportion of Māori and Pacific patients, it is also not powered to investigate differences between these patients and other subgroups in the study, and any analysis of such differences will be exploratory and hypothesis-generating in nature.

An interim analysis will be performed after 12 months of data collection (i.e. at the end of Step 2, Table 2) to verify the safety of the intervention as indicated by an absence of serious adverse events related to the bundle. We will also verify the completeness of the study data. In addition, an independent monitor will be employed to verify that the study processes do protect the rights of the participants; the reported study data are accurate, complete and verifiable from source documents; and the conduct of the study is in compliance with approved protocol/amendment(s), with Good Clinical Practice and with the applicable regulatory requirements.

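### The preferred permutation test is dropped because 120 orders are thought too few, yet 120 orders give an exact 5% test; the pooled rank sum test adopted instead, as described, is not valid for this design

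*Protocol article*

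**What the plan says.** Under Randomisation of departments: "The five departments will be sequentially allocated in a random order to the five possible dates of the bundle implementation". No restriction on the order is stated.

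Under Statistics and sample size, permutation testing is the first choice ("Although our preference would be to use permutation testing methods"), but it is set aside because "our five-cluster, five-sequence design only allows for 120 permutations", followed by "We consider this too low a number for a precise estimation of the significance of the difference between control and intervention cases". The plan therefore adopts a single Wilcoxon-Mann-Whitney (WMWU) "rank sum test as our omnibus test to ascertain whether intervention patients have significantly higher" days alive and out of hospital than control patients. It then concedes: "This WMWU test will also be sensitive to prevailing trends in patient outcomes". Quantile regressions at 0.1, 0.25, 0.5 and 0.75 follow, with DAOH90 "as the outcome, and time, intervention and site as the predictors", and the significance of the intervention term will be reported from each. Stated power, two-tailed at 0.05, is 100% for the WMWU test and 77.7% for quantile regression.

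The Discussion describes the rank sum test as one adapted to a stepped wedge and makes it the gate for the centile-by-centile reporting. The statistics section describes no such adaptation.

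**The concern.** A permutation test with few orders has a coarse p-value, not an imprecise one. When every order is listed, nothing is estimated. The only question is whether the steps are fine enough for the chosen significance level, and at 5% they are. The stated reason thus removes the one candidate test whose validity comes from the randomisation itself.

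What takes its place matters more. In a stepped wedge with one site per sequence, the first site to cross supplies mostly intervention patients and the last mostly control patients. A pooled comparison therefore mixes the treatment contrast with differences between sites and with calendar time. The Design section itself expects marked differences in practice and case mix between departments. This test decides whether the trial is called positive or negative, so its error rate is the trial's error rate.

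**Working it through.** **1. The plan's figure.** Five departments to five dates gives 5! = 120 orders, as stated.

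**2. What 120 orders allow.**
- Step size and smallest p: 1/120 = 0.0083 (2/120 = 0.0167 if a two-sided statistic ties in pairs).
- Reject if p ≤ 0.05: the 6 most extreme orders, 6/120 = 0.0500.
- Reject only if p < 0.05, which is how the article writes its alpha: 5/120 = 0.0417.

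The enumerated test was simulated on rank means adjusted for site and step (5 sites, 6 steps, about 10,984 patients, ICC 0.02, left-skewed outcome). Its size was 5.0% to 5.3%, with 3000 runs per scenario and Monte Carlo standard error about 0.4 points. One scenario combined a time trend, unequal sites and site-by-step variation.

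**3. The pooled rank sum test.** Inputs from the article: ICC 0.02, 5492 cases per group, five sites, six steps. Assumption for the hand check: equal sites, so 10,984/30 = 366 cases per site-step. The site crossing k-th has 6 − k intervention steps and k control steps, out of 15 site-steps in each condition.
- Site weights in the intervention mean: (5, 4, 3, 2, 1)/15. In the control mean: (1, 2, 3, 4, 5)/15.
- Weights in the difference: (4, 2, 0, −2, −4)/15. Sum of squares: 40/225 = 0.178.
- Between-site contribution to the variance, total variance set to 1: 0.02 × 0.178 = 0.00356.
- Patient-level contribution: 0.98 × 2/5492 = 0.00036.
- Variance that the pooled test assumes: 2/5492 = 0.00036.
- Ratio: (0.00356 + 0.00036)/0.00036 = 10.7 (from unrounded values), square root 3.28.
- Actual size of a nominal 5% test: 2 × Φ(−1.96/3.28) = 2 × Φ(−0.60) = 55%.

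This is for a difference in means. The simulated rank sum test agrees: about 54% with no time trend (3000 runs) and about 65% with a small assumed trend.

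**4. Quantile regression at 0.25**, with site and step as fixed effects and default standard errors that ignore clustering, no true effect:

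| Cluster autocorrelation (assumed) | Rejections at nominal 5% | Runs |
|---|---|---|
| 1.0 (site effects constant over time) | 5.6% | 1100 |
| 0.9 | about 10% | 1100 |
| 0.8 | 15% | 400 |

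**5. Power**, 250 runs each, at an assumed effect giving quantile regression roughly the stated power:

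| Cluster autocorrelation | Enumerated permutation test | Quantile regression |
|---|---|---|
| 1.0 | 92% | 82% |
| 0.9 | 74% | 77% |
| 0.8 | 60% | 72% |

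In the last two rows the quantile regression figure comes with inflated size. The stated 100% and 77.7% cannot be reproduced, because the site distributions behind them are not in the article.

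**The case against.** The strongest reply has four parts.

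*Too few for precision can mean p-value resolution, which is a matter of judgement.* Steps of 0.0083 are indeed coarse, and with a strict p < 0.05 rule the size is 4.2%, not 5.0%. That stands, but a coarse test of 4.2% or 5.0% size is no reason to prefer one that, as described, has a size of about 54%.

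*The quantile models include site and time, and their standard errors may be specified in a full analysis plan.* This stands too. A reader might infer that the model p-values are invalid simply because there are five clusters, or that the plan treats patients within a site-step as independent. The article supports neither. It does not state the standard-error method, and the p-values are close to nominal when site effects do not vary over time. They are unprotected against site-by-step variation, not shown to be wrong. Nor are they what directly replaced the permutation test: the WMWU test did, and it fails because it ignores site and step, which would be a fault with many clusters as well.

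*The rank sum test may be a stepped wedge version.* The Discussion says so. The statistics section calls it a single test of intervention against control patients and admits that it picks up prevailing trends, which a step-adjusted version would be built to avoid. The two descriptions conflict and need reconciling.

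*The sizes rest on inputs that the article does not give.* Outcome shape, cluster autocorrelation and trend are assumed. The 54% is the least dependent on these: it needs only the stated ICC and group sizes plus roughly equal sites, and the hand calculation gives nearly the same value.

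**Conclusion.** The concern holds in this form. The stated reason for rejecting the permutation test is wrong at the 5% level: 120 orders give an exact test of size 5.0% (4.2% under a strict inequality). The pooled rank sum test, as the statistics section describes it, is not a valid primary test. At ICC 0.02 its type I error is about 54%, so its stated 100% power has no useful meaning. That size assumes no adjustment for site or step and approximately equal site caseloads; with assumed caseload shares from 30% down to 10% the simulated figure was about 53% (400 runs). If the Discussion's adapted version is what will be run, the figure does not apply, but that version is nowhere described.

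The quantile regressions are a lesser and conditional problem. Their p-values are near nominal with constant site effects, and too small (about 10% and 15% at assumed autocorrelations of 0.9 and 0.8) if site-by-step variation exists and the standard errors ignore it.

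**What to change.** 1. Delete the statement that 120 permutations are too few.
2. Take the primary p-value from full enumeration of the 120 orders, using a rank statistic adjusted for site and step, two-sided, rejecting if p ≤ 0.05. Recompute the statistic under each order with that order's own one-week transition exclusion, so keep the excluded weeks in the dataset.
3. Reconcile the statistics section with the Discussion, so that both describe the same primary test.
4. Replace the 100% power figure with simulated power for the enumerated test, over a stated range of site-by-step variation.
5. Report the quantile regression estimates as descriptive, with intervals that allow for site-by-step correlation, and state how these are obtained. Cluster-robust errors with only five clusters would not be reliable.

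The cost is wording, a short program and a rerun of the power simulation; design and data collection do not change. The price is p-values in steps of 0.0083 and lower stated power if site-by-step variation exists: in the simulations above, 74% and 60% rather than 92%.

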What if our trial produces a negative result (i.e. no statistically significant change in DAOH_90_)? The question arises of how small a difference in DAOH_90_ actually matters? Might we miss a small difference that actually matters? The distribution of this variable is highly skewed and reflects the fact that most patients do not become infected and so will not experience any change in this outcome. We can expect the change, if it occurs, to be seen in the DAOH_90_ experienced by patients at lower centiles of the distribution. Thus, the difference may be more marked at the 25th percentile than at the 50th centile. With this in mind, our analysis will start by testing whether the distributions are significantly different or not (using a rank sum test tailored for a stepped wedge study that makes no assumptions about the nature of the distribution). If so, we will then provide numeric data on DAOH_90_ at the 10th, 25th, 50th, 75th and 90th centile and graphic representation of both distributions across the entire range to show where the effect lies. This approach avoids multiple testing and at the same time allows the maximum impact to be seen clearly without having to guess at the outset where it may lie (i.e. the 10th, the 25th or some other centile). We anticipate that this approach will mitigate the risk of missing clinically important differences between our groups.

We believe that DAOH_90_ may be a more powerful and more clinically relevant outcome measure for our study than the rate of infections per se. Nevertheless, we will utilize national databases to collect data on infections with a view to detecting any signal that will help attribute any differences in DAOH_90_ to differences in infection.

We believe the trial is well designed to test its primary hypothesis. The findings of this trial should add substantially to our understanding of postoperative infection. The trial is a direct response to the call by the World Health Assembly for new strategies “leading to strengthened infection prevention and control programmes, including… ...infection prevention practices in surgery” [5].

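### The omnibus test for the primary outcome is a pooled Wilcoxon-Mann-Whitney test that ignores site and calendar time; at the plan's own ICC its two-sided type I error is about 55%, not 5%

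*Protocol article*

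**What the plan says.** Statistics and sample size (Methods) sets permutation testing aside because five departments give only 120 orders. It then adopts a single Wilcoxon-Mann-Whitney "rank sum test as our omnibus test to ascertain whether intervention patients have significantly higher DAOH_90_ than control patients". No stratum, cluster term or time term is named.

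The next sentence concedes part of the problem: "This WMWU test will also be sensitive to prevailing trends in patient outcomes, so we will further investigate the difference using quantile regression". Those regressions, at quantiles 0.1, 0.25, 0.5 and 0.75, are fitted "with DAOH_90_ as the outcome, and time, intervention and site as the predictors". They are the only place in that section's analysis where site and time appear.

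The Discussion puts the rank test first: "our analysis will start by testing whether the distributions are significantly different or not". Centile results are to follow if it is significant. The same sentence describes the test as "using a rank sum test tailored for a stepped wedge study that makes no assumptions about the nature of the distribution", but neither section says what the tailoring is.

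On power, a 180-day step "would give us 100% power to detect a 2 DAOH difference at quantile 0.25 between groups using the WMWU", against 77.7% for quantile regression, both two-tailed at 0.05, with an ICC of 0.02 and 5492 expected cases per group.

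**The concern.** The Wilcoxon-Mann-Whitney null distribution treats patients as independent and exchangeable between the two groups. The schedule breaks both conditions.

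- **Site.** Early-switching departments dominate the intervention pool and late-switching departments the control pool. The Design section itself expects sizeable differences between departments in practice and case mix.
- **Time.** Intervention cases come later on average. Any change in length of stay, readmission or mortality over three years enters the comparison as if it were a bundle effect. The plan concedes this ("This WMWU test will also be sensitive to prevailing trends in patient outcomes") but leaves the test in its deciding position.

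A significant omnibus result could therefore arise from department mix or calendar time with no effect of the bundle, and a real effect could be masked. The plan intends to attribute a change in DAOH90 to fewer infections, and this test cannot support that step.

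**Working it through.** **Inputs from the protocol.** Five departments; six steps of 180 days, with one department switching at each step after the first; ICC 0.02; 5492 cases per group (10,984 in total); two-tailed alpha 0.05.

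**Assumptions.** Equal caseloads in the base case, because the caseload table is not readable here; random site effects; the ICC applies on a rank-like scale with total variance 1; the one-week exclusion after each switch is ignored.

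**1. The plan's own power figure.** The site distributions behind it are not given, so it can be checked only under an assumed left-skewed DAOH shape. For a 2-day difference at quantile 0.25, simulated power of the pooled test was 100% at ICC 0 and 99.8% to 100% at ICC 0.02. That agrees with the stated 100%. The 77.7% cannot be checked. Under the assumed shape, quantile regression reached 98% (60 replicates), so that shape is kinder than the plan's data.

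**2. Imbalance by site.** In switching order, the departments make up 5, 4, 3, 2, 1 fifteenths of the intervention pool and 1, 2, 3, 4, 5 fifteenths of the control pool. The contrast weights are 4/15, 2/15, 0, -2/15, -4/15. Their sum of squares is (16 + 4 + 0 + 4 + 16)/225 = 0.1778.

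**3. True against assumed variance, no effect and no trend.**
- Between sites: 0.02 × 0.1778 = 0.003556
- Within sites: 0.98 × 2/5492 = 0.000357
- Total: 0.003912
- Assumed by the test: 2/5492 = 0.000364
- Ratio: 0.003912/0.000364 = 10.7, square root 3.28

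**4. Type I error.** 2 × P(Z > 1.96/3.28) = 2 × P(Z > 0.598) = 0.55. The same formula at other ICCs gives:

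| ICC | Two-sided type I error |
|---|---|
| 0.001 | 11% |
| 0.005 | 29% |
| 0.01 | 42% |
| 0.02 (plan) | 55% |
| 0.05 | 70% |

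**5. Simulation with DAOH-like data at ICC 0.02.** Rejection was 54% and 57% in two runs with equal sites, 53.5% with unequal sites (30/25/20/15/10%), and 58% with fixed site effects and random order. False findings in favour of the bundle were 26% to 28%, against a nominal 2.5%. With strongly unequal sites (35/30/20/12/3%) the analytic rate averages 55% and ranges from 39% to 68% over the 120 orders.

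**6. Calendar time.**
- Mean step on intervention: (2×1 + 3×2 + 4×3 + 5×4 + 6×5)/15 = 70/15 = 4.67
- Mean step on control: (1×5 + 2×4 + 3×3 + 4×2 + 5×1)/15 = 35/15 = 2.33
- Gap: 2.33 steps, or 14 months

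The protocol gives no trend, so a drift has to be assumed. With no site differences and no effect, z = drift per year × (14/12)/√(2/5492), where the denominator is 0.0191:

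| Assumed drift (SD per year) | z | Rejection |
|---|---|---|
| 0.01 | 0.61 | 9% |
| 0.02 | 1.22 | 23% |
| 0.05 | 3.06 | 86% |

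A simulated drift of 0.02 SD per step gave 65% at ICC 0 and 61% to 64% at ICC 0.02. In the 64% run, 55% of all replicates falsely favoured the bundle.

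**7. Adjusted rank test on the same null data.** Least-squares regression of DAOH90 ranks on site, step and intervention rejected 5.0% at ICC 0.02, 4.5% with the 0.02 SD per step trend, and 6.0% with fixed site effects. A rank test stratified by site alone held 4% to 6% without a trend but rejected 72% to 80% with it. Both factors are needed.

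**The case against.** **The test may be adjusted.** The Discussion calls it tailored to the design, and the article condenses a fuller protocol. This does not rescue the Methods text, which names an ordinary test, justifies it, powers it and admits that it responds to trends. At the least, the two sections conflict on the primary test.

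**The quantile regressions adjust for site and time.** They do, and the 55% is the error of the omnibus step, not the rate at which an adjusted effect would be falsely reported. But they come second, at four quantiles, with none named as decisive and no rule for disagreement. A false omnibus result is not undone by them.

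**The 55% counts both directions and averages over site effects.** Correct. The plan's alpha is two-tailed, so 55% is the matching figure. False benefit alone is about 27%, roughly eleven times the nominal 2.5%.

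**The drift is an outside assumption.** Also correct, hence the range. The site result needs no drift.

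**The power figures are not hidden.** Both appear in one sentence, and the 100% is not miscalculated as far as can be seen. It is uninformative because the same test rejects about 55% of the time under no effect. The 77.7% belongs to quantile regression and cannot simply be carried over to another test.

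**Conclusion.** The point holds and must be fixed. As the Methods describe it, the deciding test for the primary outcome does not control type I error: about 55% two-sided at the plan's ICC, sample size and schedule, of which about 27 percentage points favour the bundle. Even an ICC of 0.001 gives 11%. The result rests on random site effects and on the ICC applying on a rank-like scale. The caseload shares are assumed too, but equal and unequal shares lead to the same conclusion. The effect of calendar time depends on a trend the protocol does not give, but the protocol accepts that the test is exposed to it. The 100% power figure should not be presented as the trial's power.

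**What to change.** 1. Replace the omnibus test with one that adjusts for site and for step as a six-level factor. Regressing DAOH90 ranks on site, step and intervention is preferable: it still avoids choosing a centile in advance, which is the Discussion's reason for an omnibus test. The alternative is the intervention term of the quantile regression at 0.25 with site and step as factors. Its level should be checked first: a short null run with linear time rejected 7 of 60 (11.7%), too few replicates to judge.
2. Name this as the analysis that decides the primary outcome, say how the quantile regressions relate to it, and keep the pooled test for description only.
3. Re-run the existing simulation for the chosen test, reporting type I error as well as power, with site differences, a calendar trend and site effects that vary over time, since there are only five clusters. Remove the 100%. Until that is done, 77.7% is the only power stated for an adjusted analysis.
4. Align the Methods and the Discussion so that both describe the same test.

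The cost is wording in the protocol and analysis plan and a re-run of existing code. No new data are needed. The stated power may become less favourable.
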